## Abstract

Supplemental Digital Content is available in the text

## Introduction

1

Cardiac autonomic modulation has emerged as an important marker of cardiovascular health, providing early information on impairments in cardiovascular function. Disorders in the balance between the sympathetic and parasympathetic nervous system can cause a series of cardiovascular problems. Koopman et al,^[1]^ in an epidemiological study with about 800 African adults, found that low patterns of cardiac autonomic modulation were associated with higher odds of mortality.

Likewise, physical activity has been shown to improve autonomic function.^[2]^ Indeed, several studies have shown that physically active subjects present better cardiac autonomic modulation than physically inactive peers.^[3–5]^ Rennie et al^[3]^ evaluated the practice of physical activity through a questionnaire in English individuals aged 35 to 55 years-old and observed that those subjects who were classified as practicing more vigorous intensity PA presented better autonomic modulation than those located in the lower quartiles of PA intensity. Kaikkonen et al,^[4]^ in a study with 107 obese adults, observed that higher levels of physical activity assessed by means of a questionnaire were positively associated with the SDNN index in adults in Finland. However, Kang et al,^[5]^ in a study of 131 Korean male workers, observed that physical activity recorded in the study was inversely related to cardiac autonomic modulation.

However, some limitations have been pointed-out in the literature, namely the use of only one instrument (questionnaire or accelerometer) to assess physical activity. When an accelerometer is used, although it is possible to analyze the intensity, it is unlikely that the different domains of physical activity can be analyzed without additional information. In general, the different domains of physical activity are analyzed through questionnaires, namely in the work environment, leisure, and through active transport, for example. Thus, the ideal strategy is to use both types of measures of physical activity, enabling verification of which intensity and domain of physical activity tend to be better related to cardiac autonomic modulation. It is also emphasized that men and women tend to present different cardiac autonomic modulation^[6]^ and, thus, analysis stratified by sex should be considered in this relationship.

Therefore, in the present project, we will investigate the relationship between the different intensities and domains of physical activity with cardiac autonomic modulation in adults. We hypothesize that subjects who perform physical activity at higher intensities will present better cardiac autonomic modulation. Considering the different domains of physical activity, our hypothesis is that physical activity in leisure has a greater relationship with autonomic cardiac modulation as it is carried-out in the free time period when the individual is more likely to be free from work stress and/or because it is, generally, an activity which the subject enjoys practicing.

## Materials and Methods

2

This is a cross-sectional study funded by the São Paulo Research Foundation (FAPESP, process number 2017-07321-9). The protocol registration of this research is available at ClinicalTrials.gov (NCT03986879). The study procedures will take place from November 2018 until the second semester of 2020.

### Ethical aspects

2.1

The study was approved by the Ethical Research Committee from Sao Paulo State University – Unesp, at protocol CAAE: 72191717.9.0000.5402. All the subjects who agreed to participate will sign an Informed Consent Term – Appendix 1, with all information about the research procedures and requirements, being free of any form of charge or payment, and free to desert from research at any time.

### Sample

2.2

The sample will include adults aged 18 years or older from the city of Santo Anastacio, located in the southeastern region of Brazil, who are not injecting any type of medicine to control heart rate. Considering that the approximate population with over 18 years of age in the city of Santo Anastacio is 16000 inhabitants (IBGE), a correlation value of r = 0.23 was adopted to calculate the sample size,^[4]^ with an 80% power and 5% alpha, which determined a minimum sample size of 147 subjects.^[7]^ However, predicting possible refusals to participate in the study and losses of the subjects and data, a further 30% was added to the sample, totaling a minimum of 192 subjects to be evaluated. Conversely, as the present study will consider age, sex, and socioeconomic condition as adjustment variables, more 20 subjects was added for each adjustment variable. Thus, the final sample estimated is 252 individuals to be evaluated. The equation below was used to calculate the sample size. 
[figure not shown]

where n = sample size; Zα / 2 = alpha error value (1.96 [5%]); Zβ = beta error value (0.84 [20%]); r = correlation coefficient (Pearson or Spearman).

For sampling, the city of Santo Anastacio will be divided according to census sectors delimitation. This city has a total of 34 census sectors, of which 23 are in the urban area of the city and will be contemplated in this study. The number of people to be interviewed in each of the census tracts will be calculated based on the number of people residing in these sectors, considering the proportional population of each census sector – Table 1. In order to carry out this procedure, the census tracts will be divided based on a geographic map of the city of Santo Anastacio – Figure 1. The neighborhoods will be registered and numbered, as well as the streets and households. Subsequently, the neighborhoods, streets, and homes will be randomly drawn based on the “random” function of SPSS. Residents of the randomly selected households aged 18 or over will be considered eligible to participate in the study and invited to participate. If the selected individuals decline to participate in the research, a new household will be randomly selected, until complete the minimum sample size required for each census sector. This sample selection design was based on the 1st Design of the National Health Survey sample.^[8]^

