### Data collection

2.3

Initially, the evaluators will visit the census sectors drawn and the households that will be part of the sample. In this first evaluation, a face to face interview will be performed using an electronic questionnaire. The questionnaire contains physical activity domains as well as socio-demographic characteristics. After the participants have completed the questionnaires, an accelerometer will be delivered to the research participant with explanations about its use (5-day period). On a pre-scheduled date, the evaluator responsible for delivering the accelerometer will visit to the residence of the participant and perform the accelerometer recall. At that time, the evaluation of cardiac autonomic modulation through analysis of heart rate variability will be scheduled at a predetermined location, being the participant informed about the previous recommendations for this measure procedure – Figure 2.

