### Cardiac autonomic modulation

2.6

The evaluation of cardiac autonomic modulation will be performed through HRV. For this evaluation, subjects will be instructed not to ingest alcoholic beverages and/or stimulants, such as coffee and tea, for 12 hours prior to the experimental protocol, to avoid influences on cardiac autonomic behavior.^[16]^

For this analysis, heart rate will be recorded beat-by-beat, using an Heart Rate Monitor (Polar V800, Finland), for 30 minutes at rest in a supine position, maintaining spontaneous breathing, in a room with a temperature between 21 and 24°C and relative air humidity between 50 and 60%.^[16]^ Only circulation of the evaluators will be allowed in the room during the execution of the HRV collection.

In the series of RR intervals obtained, 1000 intervals of the most stable stroke period will be analyzed, followed by digital filtering complemented by manual filtering to eliminate ectopic, artifacts, and premature beats. Only series with more than 95% sinus beat will be included in the study.^[17]^ The HRV analysis will be performed using linear methods (time and frequency domains) and non-linear methods.

For HRV analysis using linear methods, the RMSSD (square root of the square mean of the differences between adjacent normal RR intervals in a time interval expressed in milliseconds) and SDNN (standard deviation of the mean of all normal RR intervals, expressed in miliseconds) will be used for time domain analysis.^[18]^ For the analysis of HRV in the frequency domain, the spectral components of low frequency (LF: 0.04–0.15 Hz) and high frequency (HF: 0.15–0.4 Hz) will be used, in milliseconds squared (ms^2^) and normalized units (nu), as well as the ratio between these components (LF/HF). The spectral analysis will be calculated using the fast Fourier transform algorithm.^[18]^

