### Statistics analysis

2.8

After verification of normality by Shapiro-Wilks test, the variables characterizing the sample will be expressed as mean and standard deviation or median and interquartile range. The dependent variable will be the cardiac autonomic modulation. Pearson or Spearman correlation will be used to analyze the relationship between cardiac autonomic modulation and physical activity. Linear regression will evaluate the magnitude of the relationship between cardiac autonomic modulation and physical activity, both in the unadjusted model and in models adjusted by age, schooling, ethnicity, and socioeconomic status. Confounding variables will be inserted simultaneously into the model. It should be emphasized that linear regression analysis will be performed stratifying the study participants by sex. This same type of analysis will be performed to verify the possible relationships between the different domains of physical activity (work, leisure, and displacement activity) and cardiac autonomic modulation.

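### As worded, the medication criterion excludes only injected heart-rate medicine, so oral users remain eligible for a study whose outcome is heart-rate variability

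*Protocol article*

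**What the plan says.** Section 2.2 (Sample) of the protocol article states one medication criterion. Participants are adults from the city "who are not injecting any type of medicine to control heart rate". Later in the same section the household rule is given by age alone: "Residents of the randomly selected households aged 18 or over will be considered eligible to participate in the study and invited to participate".

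Section 2.8 (Statistics analysis) defines the outcome: "The dependent variable will be the cardiac autonomic modulation". Section 2.6 shows that all of its indices (time domain, frequency domain and Poincaré plot) come from a beat-by-beat heart-rate recording. The regression is run "both in the unadjusted model and in models adjusted by age, schooling, ethnicity, and socioeconomic status", separately by sex.

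Three other statements bear on the point:

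- Section 2.3 (Data collection), on the interview: "The questionnaire contains physical activity domains as well as socio-demographic characteristics".
- Section 2.6, on preparation for the recording: "subjects will be instructed not to ingest alcoholic beverages and/or stimulants, such as coffee and tea, for 12 hours prior".
- Section 2.6, on signal quality: "Only series with more than 95% sinus beat will be included in the study".

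**The concern.** The evident purpose of the criterion is to keep drug-altered heart rate out of an outcome built from heart rate. Route of administration has no bearing on that purpose, yet the sentence selects by route. An evaluator who follows it to the letter would enrol someone taking a heart-rate medicine by mouth.

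The study's aim is the association between physical activity and variability. If users of these medicines differ from non-users in activity and also in variability, the mixture of the two groups adds a component to the observed correlation that has nothing to do with activity. It could create an apparent association or hide a real one, depending on whether the two shifts run in the same or in opposite directions.

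**Working it through.** **1. Does any other statement close the gap?**

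| Place | What it controls | Deals with oral heart-rate medicine? |
|---|---|---|
| 2.2, household eligibility | Age 18 or over | No |
| 2.3, questionnaire summary | Activity domains, socio-demographics | Not mentioned; the instrument is not shown |
| 2.6, preparation | Alcohol and stimulants for 12 hours | No |
| 2.6, signal quality | More than 95% sinus beats | No; it screens rhythm, not medication |
| 2.8, adjustment | Age, schooling, ethnicity, socioeconomic status; stratified by sex | No |

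Nothing in the text excludes oral users or adjusts for their use.

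**2. The plan's own figures.** Inputs from section 2.2: r = 0.23, Z values 1.96 and 0.84. The formula is not shown in the text available, so the standard Fisher z form is assumed: n = ((1.96 + 0.84)/atanh(0.23))² + 3 = (2.80/0.2342)² + 3 = 145.9. With unrounded Z values it is 146.1, which rounds up to the stated 147. Then 147 × 1.3 = 191.1, i.e. 192, and 192 + 3 × 20 = 252. The stated figures reproduce. The present point changes none of these inputs, so there is no corrected sample size.

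**3. How large could the bias be?** The documents give neither the share of users nor their differences from non-users, so these are assumptions: share p = 5-15%; mean shift d = 0.5-0.8 within-group SDs in size, the same for activity and variability.

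With within-group correlation r₀, the correlation in the mixed sample is

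r_obs = (r₀ ± p(1−p)d²) / (1 + p(1−p)d²),

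with plus if both shifts have the same sign and minus if they oppose.

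No true association (r₀ = 0):

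| p | d | p(1−p)d² | Size of spurious r | Share of 0.23 |
|---|---|---|---|---|
| 0.05 | 0.5 | 0.0475 × 0.25 = 0.0119 | 0.0119/1.0119 = 0.012 | 5% |
| 0.10 | 0.5 | 0.09 × 0.25 = 0.0225 | 0.0225/1.0225 = 0.022 | 10% |
| 0.15 | 0.8 | 0.1275 × 0.64 = 0.0816 | 0.0816/1.0816 = 0.075 | 33% |

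The division matters at the top of the range: without it the last row would read 0.082.

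True within-group correlation of 0.23:

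- p = 0.05, d = 0.5: (0.23 ± 0.0119)/1.0119 = 0.216 (opposing) or 0.239 (matching).
- p = 0.15, d = 0.8: (0.23 ± 0.0816)/1.0816 = 0.137 (opposing) or 0.288 (matching).

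**4. What that does to a test.** This assumes that all 252 are analysed together, with two-sided 5% and Fisher z, so the standardised value is atanh(r) × √249, where √249 = 15.78.

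- No true association, p = 0.10, d = 0.5: the false-positive rate is about 6%, close to nominal.
- No true association, p = 0.15, d = 0.8: 0.0756 × 15.78 = 1.19. The upper tail is 1 − Φ(1.96 − 1.19), about 22%, and the lower tail is negligible.
- True r = 0.23 with no users: power is about 96%. With opposing shifts it is about 93% at the low corner (r = 0.216) and about 59% at the high corner (0.137 gives 0.1381 × 15.78 = 2.18, and Φ(2.18 − 1.96) = 0.59).

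All of these are for the unadjusted correlation.

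**5. Participants affected.** 0.05 × 252 = 12.6 and 0.15 × 252 = 37.8, so about 13 to 38 people.

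**The case against.** The strongest reply is that *injecting* is a language slip for *ingesting*. An injection-only rule makes little sense as a deliberate choice, section 2.6 uses the verb *ingest* when it describes preparation for the recording, and the article has other awkward phrasing. On that reading oral users are excluded and no bias arises from this source. This is probable and it stands as a limit on the point. It does not rescue the text: the published criterion still says something else, and staff or readers who follow it would admit oral users.

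The second reply is that bias is not shown. That also stands. It needs users to differ in activity as well as in variability, and the documents give no figure for either. Adjustment for age and the other covariates would remove part of it. The top of the range needs the highest assumed prevalence together with the largest assumed shift in both variables.

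A reader might infer three further things that the article does not support:

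- That medicine use is not recorded. Section 2.3 summarises the questionnaire in one sentence and a journal article condenses, so the absence of such an item cannot be established.
- That diagnosed heart disease ought to be in the model. That is a separate covariate preference and does not follow from this wording.
- That the existing replacement rule already makes up for extra exclusions. Section 2.2 triggers it only when selected people decline, not when they are found ineligible.

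**Conclusion.** The criterion is wrong as written: it selects by route where its evident purpose concerns the effect on heart rate, and nothing else in the article excludes oral users or adjusts for their use. It is tempting to conclude that oral users are being enrolled and that the results are confounded. The documents do not support that. They do not show how the rule is applied, and the bias is a risk, not a finding.

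If the word is a slip and oral users are kept out, this is a text correction and nothing more. If the rule is applied literally, the spurious correlation runs from about 0.01 to 0.075 in either direction, i.e. from negligible to about a third of the planning value. That range rests on 5-15% users and 0.5-0.8 SD shifts in both variables, all assumed, and is before covariate adjustment. The low cost of the correction justifies making it without settling where in the range the truth lies.

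**What to change.** - Reword the criterion in section 2.2 so that it covers use, by any route, of medicine that controls heart rate. This is one sentence and serves under either reading of the present text.
- Extend the household replacement rule to people found ineligible as well as those who decline. The cost is some additional households to visit.
- Establish how the criterion has been applied since procedures began in November 2018. If anyone was enrolled under the literal wording and their medicine use is known or can be obtained, report the main association with and without them. The analysis without them loses about 13-38 of 252 under the assumed prevalence, leaving about 239 to 214 before other losses. If use was not recorded, participants would have to be asked again. If oral users were excluded all along, this step is not needed.

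### The household-based, multistage draw can enrol several adults per home, but the sample size and the stated analyses make no allowance for clustering, so standard errors are likely too small by an unknown amount

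*Protocol article*

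**What the plan says.** **Design (Protocol article, section 2.2 Sample).** All 23 urban census sectors are included, and the number of people per sector is set in proportion to its population. Within sectors, "Subsequently, the neighborhoods, streets, and homes will be randomly drawn". On who is then approached, the article says: "Residents of the randomly selected households aged 18 or over will be considered eligible to participate in the study and invited to participate". If there is a refusal, a further household is drawn until the sector's quota of people is met. The quota is counted in people, but the unit drawn and replaced is the home.

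**Size (same section).** The article reports that "a correlation value of r = 0.23 was adopted to calculate the sample size", "with an 80% power and 5% alpha, which determined a minimum sample size of 147 subjects". Then "a further 30% was added to the sample, totaling a minimum of 192 subjects to be evaluated", and 20 more subjects are added for each of three adjustment variables, giving 252.

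**Analysis (section 2.8 Statistics analysis).** Pearson or Spearman correlation is planned, and "Linear regression will evaluate the magnitude of the relationship between cardiac autonomic modulation and physical activity", both unadjusted and adjusted, with the regressions stratified by sex. The section mentions no household, street or sector term, no clustered variance and no weights.

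**The concern.** People who share a home or a street may resemble each other both in physical activity and in heart rate variability. Socioeconomic class is scored partly on rooms and household assets (section 2.7), so housemates share much of that covariate. Neighbours share the surroundings in which the walking and cycling of the displacement domain take place. Where both the exposure and the outcome residual are alike within a cluster, a standard error that assumes independence is too small. Confidence intervals are then too narrow, and a test run at 5% rejects more often than 5% of the time. A sample size computed for independent observations also buys less information than its head count suggests.

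**Working it through.** **1. Does the stated size contain a design effect?** Inputs from section 2.2: r = 0.23, z = 1.96 for alpha, z = 0.84 for beta.

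- Fisher z of 0.23: atanh(0.23) = 0.2342.
- ((1.96 + 0.84) / 0.2342)² = 142.9.
- Adding 4 gives 146.9, rounded up to 147. Adding 3 gives 145.9, rounded up to 146, or 147 with unrounded z values.
- 147 × 1.30 = 191.1, rounded up to 192.
- 192 + 3 × 20 = 252.

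The plan's figures are reproduced. Every increment is accounted for by losses or covariates, and none is for clustering.

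**2. How large could the effect be?** For a slope or correlation, an approximate variance inflation is

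inflation = 1 + (m − 1) × ICC(exposure) × ICC(outcome residual),

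where m is the number of participants per cluster and ICC is the intraclass correlation. The article gives none of these three, so the values below are assumptions. The true two-sided error rate at nominal 5% is 2 × (1 − Φ(1.96 / √inflation)). The naive standard error is too small by 1 − 1/√inflation.

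| Assumed cluster | ICC exposure | ICC residual | Inflation | True SE / naive SE | Naive SE too small by | True alpha | 147 becomes |
|---|---|---|---|---|---|---|---|
| Home, m = 2 | 0.1 | 0.1 | 1.01 | 1.005 | under 1% | 5.1% | 149 |
| Home, m = 2 | 0.3 | 0.3 | 1.09 | 1.044 | 4% | 6.0% | 161 |
| Home, m = 2 | 0.5 | 0.3 | 1.15 | 1.072 | 7% | 6.8% | 170 |
| Home, m = 3 | 0.3 | 0.3 | 1.18 | 1.086 | 8% | 7.1% | 174 |
| Home, m = 3 | 0.5 | 0.3 | 1.30 | 1.140 | 12% | 8.6% | 192 |
| Street, m = 5 | 0.2 | 0.2 | 1.16 | 1.077 | 7% | 6.9% | 171 |

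Worked example, fifth row: 1 + 2 × 0.5 × 0.3 = 1.30; √1.30 = 1.140; 1 − 1/1.140 = 0.12; 1.96/1.140 = 1.72, which gives a two-sided rate of 8.6%.

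**3. Power.** At inflation 1.30, power for r = 0.23 with 147 analysed falls from 0.80 to 0.69. With all 252 analysed in one pooled analysis it is still about 0.90. The reserve over 147 therefore covers power in a pooled analysis if few are lost. It does nothing for the error rate or the interval width.

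**4. What lowers the effect.**

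- In a sex-specific regression a man and a woman from one home fall into different models. A home with one of each contributes m = 1 to each model, and its inflation is 1. Same-sex housemates and street neighbours remain clustered. Section 2.8 states sex stratification for the regressions, not for the correlations.
- Adjusting for socioeconomic status and schooling removes part of what housemates share in the residual. The unadjusted models and the correlations keep it.
- Sectors are strata with proportional allocation. Ignoring strata tends to make standard errors slightly too large, which works the other way.

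**The case against.** The strongest reply is that the article does not exclude a proper analysis. Linear regression can be fitted with clustered variance, an article commonly leaves such detail to a fuller plan, and the size of the problem rests wholly on assumed values. It may be negligible: the range starts at 1.01, and the 1.30 case needs three enrolled adults per home throughout, which in a sex-specific regression means three of the same sex.

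Much of this stands. It limits how strongly the point can be put, but it does not remove it. The sample size is fixed in this article and assumes independence, while the same section describes a draw that can break it. The methods section is explicit about covariates and sex stratification, and its methods, taken as stated, ignore the clustering.

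A reader might infer more than the text supports:

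- **That every adult in each drawn home is enrolled.** The text makes adult residents eligible and invites them, but the next sentence speaks of selected individuals who decline. It names no one-per-home step, yet it does not say that all are enrolled. The national survey design on which it is based is cited, not described.
- **That the standard errors are shown to be wrong.** If either intraclass correlation is zero, the inflation is 1. The text supports only that they are likely too small.
- **That the sectors are clusters of about 11 (252/23).** All urban sectors are included, so they are strata.
- **That homes on short streets are over-represented.** This holds only if streets are drawn first and with equal probability, which the article does not say. Unequal selection also does not by itself bias a slope.

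**Conclusion.** The point holds in a moderate form. The design allows several participants from one home and several homes from one street, the size has no design effect, and the analyses are stated without any allowance for clustering. Standard errors are therefore likely too small, by an amount that the article does not allow one to compute. Under the assumed 2 to 3 adults per home and intraclass correlations of 0.1 to 0.5, the variance inflation is about 1.01 to 1.30 and the true two-sided alpha about 5.1% to 8.6%. The upper end is a corner case. The pooled correlations and any street-level clustering are the most exposed; the sex-stratified regressions are less so. The main consequence is for error rates and intervals, with power secondary. The remedy is cheap enough to be worth making although the size is uncertain.

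**What to change.** - State how many adults per home may be enrolled and how they are chosen.
- Keep household and street identifiers in the analysis file.
- Fit the regressions with cluster-robust or survey variance. Use the household as cluster, or the street if it is the first-stage unit, and the census sector as stratum.
- Take the p-values for the correlations from standardised slopes in the same model, so that correlations and regressions rest on the same variance.
- Add a sentence to the sample size paragraph saying that the 147 assumes independent observations.
- Selection weights are at most an optional sensitivity analysis, and only if the selection probabilities can be reconstructed.

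**Cost.** Section 2.2 already has streets and households registered and numbered, so no new sampling or measurement is needed. The change is an option in the regression command and two columns in the data. The downside is slightly wider intervals.
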